## Abstract

**Background:**

Cancer survival comes at a price: pediatric cancer survivors bear a high risk for a wide range of cognitive difficulties. Therefore, interventions targeting these difficulties are required. The aim of the present clinical trial is to extend empirical evidence about efficacy of cognitive and physical training in pediatric cancer survivors. It is hypothesized that early cognitive and physical interventions affect the remediation of pediatric cancer survivors in terms of improved executive functions (primary outcome). Additional positive effects of cognitive and physical intervention to other areas such as memory and attention are expected (secondary outcome). Changes in cognitive performance are expected to be associated with structural and functional changes in the brain.

**Methods:**

Overall, 150 pediatric cancer survivors and 50 matched controls will be included in this trial. The cancer survivors will be randomly assigned to either a computerized cognitive training, a physical training (exergaming) or a waiting control group. They will be assessed with neuropsychological tests, tests of sport motor performance and physical fitness before and after 8 weeks of training and again at a 3-months follow-up. Moreover, neuroimaging will be performed at each of the three time points to investigate the training impact on brain structure and function.

**Discussion:**

With increasing cancer survival rates, evidence-based interventions are of particular importance. New insights into training-related plasticity in the developing brain will further help to develop tailored rehabilitation programs for pediatric cancer survivors.

**Trial registration:**

KEK BE 196/15; KEK ZH 2015–0397; ICTRP NCT02749877; date of registration: 30.11.2016; date of first participant enrolment: .18.01.2017.

## Background

Cancer is the leading cause of death by disease in children and adolescents aged 5–15 years [1]. Advances in early diagnosis and improved treatment approaches have led to an increase in long-term survival rates of up to 80% [2]. However, survival of pediatric cancer comes at a price: An increasing amount of literature indicates that the most frequent pediatric cancer diagnoses are associated with late effects including neurocognitive deficits and intellectual decline (e.g., [3–5]).

Cognitive functioning in pediatric cancer is affected by complex interactions between several factors such as age at onset or treatment modality (for review see [6]). For example, younger age at diagnosis and at treatment of central nervous system (CNS) tumor is associated with greater cognitive problems indicating that sequelae of cancer and treatment depends on the developmental status of the child [7]. The most common treatment for pediatric cancer include surgery, chemotherapy, and radiation therapy. All of these treatments do not solely target malignant cancer cells, but entail harmful effects to multiple organ systems, including the CNS [4]. Treatment related side effects such as neurotoxicity [8, 9] seem to be particularly harmful to specific cognitive processes such as the executive functions (EF) [10–12].

EF are of particular importance for academic achievement with executive dysfunction having far reaching consequences on survivors’ scholastic career and overall quality of life [13, 14]. There are three core EF (inhibition, shifting and working memory) that build the basis for higher order cognitive functioning such as planning or problem solving [15, 16]. Impairments in EF at an early stage after diagnosis will put the patients at risk to academically fall behind peers [3, 17, 18]. Thus, research recently focuses on developing adequate intervention and rehabilitation programs with the aim to alleviate cognitive impairments, facilitate the return to school and improve the long-term quality of life of pediatric cancer survivors (e.g., [4]). Although the neurocognitive impairments in pediatric cancer survivors imply the necessity to intervene as early as possible [6, 18], until now only very few intervention studies in this population are available.

Cognitive training programs have been used to address core cognitive deficits in a variety of individuals with developmental difficulties. Home-based, computerized cognitive training carries a minor burden because it can be completed flexibly at any time at home without adverse side effects [19]. Computerized cognitive training (e.g., Cogmed RM® [20]) is often based on a core cognitive function such as i.e. working memory and follows the assumptions that through repeated and intensive practice cognitive capacity can be increased. Several studies investigated the efficacy of such a working memory training in children and adolescents with atypical development such as attention deficit hyperactivity disorder (e.g., [20, 21]), traumatic brain injury, stroke [22, 23] or very preterm-born children [24]. There is supporting evidence for improvements on tasks that resemble the training task (near-transfer effects) following working memory training. However, transfer effects to other untrained cognitive domains (far transfer effects) are currently subject to a controversial debate (for more information see [25–28]).

Studies investigating working memory training in pediatric cancer survivors revealed promising results (for review see [5]). Hardy and colleagues showed significant improvement in visual working memory and in parent-rated learning problems in a pilot study with 20 pediatric cancer survivors after working memory training when compared to an active control group undergoing a non-adaptive intervention [29]. Working memory trainings, such as Cogmed RM®, were found to be feasible and a viable option to address cognitive late effects among pediatric cancer survivors [19, 30]. Although there are first encouraging results regarding working memory training, yet data are too limited to form “best practice” guidelines [5].

Physical exercise seems to be another promising approach to foster cognitive performance. Many studies indicate that physical exercise can have positive effects on a range of cognitive functions in typically developing children and adolescents [31–33]. Regularly performed physical exercise can alter brain functions responsible for cognition and behavior [31, 34, 35]. In particular, EF seem to benefit from physical training (e.g., [36–38]). Recently, there has been an increasing interest in qualitative factors of physical exercise such as cognitive engagement (e.g., [39–41]), because they likely influence cognition in a positive way [32, 39, 42]. A recent study was able to demonstrate that a 6-week cognitively demanding sports game intervention for school children, but not a pure endurance training, yielded significant intervention effects on shifting, a core dimension of EF [43]. The underlying assumption is that cognitively engaging physical activities also train brain regions that are used to control higher order cognition [34, 42, 44]. Hence, physical exercise should ideally not only challenge the body but also the mind.

An innovative combination of a physically and cognitively demanding training at home can be achieved with exergaming [45]. Exergaming is a portmanteau of “exercise” and “gaming” [46], which enables individuals to physically interact with a virtual environment. In a gamified fashion, the individual has for example to avoid obstacles without touching them by jumping from left to right. The quantitative (intensity, duration = e.g., faster obstacles) and qualitative physical exercise characteristics (modality = e.g., jumping, running) can be modulated, allowing to go “beyond simply moving to moving with thought” [47]. Up to date, there are few studies investigating the relationship between exergames and cognition [37, 41, 48–51]. In pediatric cancer survivors, first positive results of physical exercise on quality of life, body composition and physical activity have been described [52, 53]. However, high quality studies including larger samples are needed [52, 54]. Although exergaming enables a training under highly controlled conditions at home, to our knowledge, no study to date examined the impact of physical exercise or exergaming on cognitive performance in pediatric cancer survivors.

The literature suggests that training related changes in brain structure and function can occur with cognitive and physical training [35, 55]. Although there seems to be evidence that they might facilitate a positive effect on cognition, the underlying mechanisms remain unclear. Brain imaging therefore might be a valuable method to identify neuronal effects following working memory training or physical exercise. In adults, studies on working memory training and physical exercise revealed brain changes in structure and function (for reviews see [35, 55]). There is, evidence for increases of brain activation (stronger neural response and greater task related activity), decreases of brain activation (increased neuronal efficiency) or a combination of both [55]. Furthermore, there seems to be an increased functional connectivity for example in the default mode network and in the executive network following physical exercise [56]. Studies on both, working memory training and physical exercise, detected an increase in cerebral blood flow following training [35, 55]. Besides functional changes, structural changes in gray or white matter have been found. However, there seems to be no clear single pattern of results regarding the neural effects of cognitive and physical training, pointing towards highly dynamic plastic processes underlying cognitive change [55].

In pediatric cancer survivors, only very few studies on working memory training or physical exercise are available. A study on working memory training suggests alterations in the functional network of working memory [30] while physical exercise has an impact on white matter and hippocampal volume [57]. However, the relationship between cognitive or physical training and neuroplasticity in pediatric cancer is far from understood. Therefore, more studies are needed to investigate the neural mechanisms of training.

### Study aims and hypotheses

The purpose of this study is twofold: First, the availability of well-designed, child-friendly, and evidence-based training is of major clinical relevance and will contribute to the prevention of a further decline of cognitive functions and scholastic problems. Therefore, this study will compare the efficacy of two different trainings aiming to foster cognitive performance in pediatric cancer survivors. As primary outcome, we hypothesize that both trainings (computerized working memory training and exergaming) lead to improvements in core EF performance (inhibition, shifting and working memory) compared to a control condition. As secondary outcome, near and far transfer effects of both trainings are expected immediately after the training and at 3-months follow-up.

Second, the detection of training-induced changes in brain structure and function will give insight into the training related plasticity of the child’s brain. As further secondary outcome, the relationship between training related cognitive change and training related change in brain structure and function will be examined.

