### Participants

#### Cancer survivors

In total, 150 children and adolescents aged 7–16 years with a previous diagnosis of cancer with or without CNS involvement (CNS+ and CNS-) in the past ten years and terminated their treatment (surgery, radiation, and/or chemotherapy) at least 12 months prior to participation will be included in the study. Cancer survivors will be recruited at two specialized pediatric university hospitals in Zurich and in Bern, Switzerland. To reduce the heterogeneity of the sample, participants with a history of cancer without CNS involvement and only surgical removal of the tumor without subsequent radiation and/or chemotherapy will be excluded from the study. The sample size was calculated for the primary outcome measures of inhibition, shifting (Color-Word Interference Test; retest-reliability = .77) and working memory performance (Block Recall Test; retest-reliability = .62), both will be assessed before and after the trainings and before and after the waiting period. Sample size calculation was performed using G*Power 3 [58], based on a repeated measures ANOVA with small effect sizes (six groups; two time points; statistical power = 80%; *α* = 0.05), resulting in a minimal sample size of 14 (for inhibition, shifting) and 22 (for working memory) in each group. In order to compensate for losses/drop outs, sample size was defined at 25 patients per group.

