### Data analysis

The data collected will be tested as to their statistical properties and analyzed accordingly. The level of significance is set to *α* = 0.05. Normally distributed background and control variables will be compared between the groups (experimental vs. control group) using two-sample *t*-tests, and variables without normal distribution will be tested using Wilcoxon rank-sum test. Chi-squared test will be used for categorical variables. The diary entries and the execution data obtained from the XBOX/ Cogmed RM® during training sessions will be used to provide information about the focus and the frequency of the training. These scores will be presented as descriptive summaries. The frequency and duration of exercises during the intervention period will then be compared between the experimental groups.

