#### Behavioral data

Raw scores of cognitive tests will be transformed to standard scores, *T*-scores or Intelligence quotient (IQ)-scores using age norms from the respective test manuals. Subsequently, to make results comparable among different tests, *z*-scores will be computed. In order to compare the baseline performance between patients and controls, Analyses of Variance (ANOVAs) will be calculated. To examine training effects, primary and secondary outcome variables of T1, T2 and T3 will be analyzed using Analysis of Covariance (ANCOVA) comparing the three groups, in order to increase statistical power and reduce possible bias [83]. To test whether inter-individual differences predict training or transfer effects, linear regression analyses will be performed (predictor variables i.e. gender, age, kind of cancer, cancer treatment methods, IQ).

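### Three co-equal primary outcomes share an unadjusted 0.05 with no rule for primary success: about 11–14% family-wise error if any one outcome counts

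*Protocol article*

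**What the plan says.** Study aims and hypotheses states the primary hypothesis: both trainings "lead to improvements in core EF performance (inhibition, shifting and working memory) compared to a control condition". The Abstract names executive functions as the primary outcome, but no composite score is defined. The Cancer survivors section treats the components as separate measures: "The sample size was calculated for the primary outcome measures of inhibition, shifting" (both from the Color-Word Interference Test, retest reliability .77) and working memory (Block Recall Test, .62). It gives 14 and 22 per group for six groups, two time points, 80% power and α = 0.05, and raises both to 25.

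Data analysis says "The level of significance is set to *α* = 0.05" and mentions no division of that level. Behavioral data says that "primary and secondary outcome variables of T1, T2 and T3 will be analyzed" by an ANCOVA comparing the three groups. It names no contrasts with the waiting control group.

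**The concern.** Three outcomes are offered as primary on equal terms, each sized and tested at the full 0.05, with nothing fixing how many must succeed. One significant subtest out of three could then be reported as the trial meeting its primary hypothesis, and that claim would not carry a 5% error rate.

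There is a second gap. The hypothesis is about each training against control, while the stated test asks whether the three groups differ at all. A significant result can come from working memory training differing from exergaming, with neither shown to beat control. Contrasts with control are needed to support the claim, and the article does not say at what level or after what gate they would be tested.

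**Working it through.** **Inputs.** From the article: three primary outcomes; three randomised arms of 50 (25 CNS+ and 25 CNS− each), here A = working memory training, B = exergaming, C = waiting control; α = 0.05; retest correlations .77 and .62. Assumed: correlations between outcomes of 0 to 0.7, because none is given, and effect size f = 0.14, because the article says only that effects are small.

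**1. The plan's own sample size.** For the within-between interaction with k = 6 groups and m = 2 times, λ = f²·N·m/(1 − ρ), with df = (k − 1)(m − 1) and (N − k)(m − 1).
- Inhibition, shifting: n = 14, N = 84, λ = 0.0196 × 84 × 2/0.23 = 14.3, power 81.8% (78.1% at n = 13).
- Working memory: n = 22, N = 132, λ = 0.0196 × 132 × 2/0.38 = 13.6, power 80.7% (78.5% at n = 21).

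So f = 0.14 at an unadjusted 0.05 reproduces 14 and 22 exactly; f = 0.10 gives 26 and 42. On this reconstruction no share of alpha was set aside for having three outcomes.

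**2. Error rate if any one outcome counts.** Three independent F tests: 1 − 0.95³ = 14.3%. Six independent contrasts: 1 − 0.95⁶ = 26.5%, which is lower in practice because the control group is shared. Simulation with no true effects, 50 per arm, 100,000 trials:

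| Outcome correlation | Any of three F tests at 0.05 | Any of six contrasts (A–C, B–C) at 0.05, either direction | The same, favouring a training only | Any of three F tests at 0.05/3 |
|---|---|---|---|---|
| 0 | 14.1% | 24.7% | 12.8% | 4.9% |
| 0.3 | 13.6% | 23.7% | 11.9% | 4.9% |
| 0.5 | 12.7% | 21.8% | 10.9% | 4.5% |
| 0.7 | 11.3% | 19.4% | 9.6% | 4.0% |

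The first rate column is the analysis as written. The next two add contrasts that the article does not specify. If contrasts were tested only after a significant F test at 0.05, the rate would be about 12% to 11% in either direction and about 6% to 5% favouring a training (correlation 0 to 0.5).

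**3. A procedure that holds 5%.** With three arms, once the hypothesis that all arms are equal is false, at most one of the three pairwise equalities can be true. Testing pairs at level a only after an F test at level a therefore keeps the error within one outcome at a or below. With a = 0.05/3 for each of three outcomes, the total is at most 0.05.

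The demanding case is that A works on all outcomes and B equals C on all. The chance of a false B–C claim is then at most 1 − (1 − 0.05/3)³ = 4.9%; simulation gives 3.9–4.9%. If the level instead rises by Holm (0.05/3, 0.05/2, 0.05) and pairs are tested at the risen level, the same case gives up to 1 − 0.9833 × 0.975 × 0.95 = 8.9%. Simulation with a large A effect gives 6.8–8.5%.

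**4. Cost in power.** The pairwise detectable difference scales by (2.394 + 0.842)/(1.960 + 0.842) = 3.236/2.802 = 1.155. In the plan's own calculation at f = 0.14, a level of 0.05/3 needs 18 and 28 per group. At 25 per group (N = 150):
- Working memory: λ = 0.0196 × 150 × 2/0.38 = 15.5; power falls from 86.4% to 74.4%.
- Inhibition, shifting: λ = 0.0196 × 150 × 2/0.23 = 25.6; power falls from 98.3% to 95.4%.

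These are before dropout, and they apply to the six-group interaction that was sized, not to the three-group ANCOVA.

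**The case against.** The article condenses a fuller protocol, and a multiplicity rule or follow-up contrasts may stand in an analysis plan that is not shown. Their absence alone would be no finding. What remains is what the article fixes: separate primary measures, each sized at the full 0.05, and one significance level of 0.05. That sizing fits an any-outcome rule only if the inflation is accepted, and it gives no assurance of 80% power under an all-outcomes rule.

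The hypothesis can also be read as a conjunction: both trainings improve all three functions. If all six contrasts had to be significant, the error with no true effects would be below 0.1% at correlations up to 0.7. That reading is possible, and nothing in the text excludes it. Nothing adopts it either, which is why a rule is needed.

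A reader might infer that the chance of a false primary success is about a quarter. The document does not support that. It specifies "will be analyzed using Analysis of Covariance (ANCOVA) comparing the three groups", not six contrasts each at 0.05. The larger rate also counts results in which training looks worse than control, whereas the hypothesis concerns improvement. Errors favouring a training are about 10–13% even with six ungated tests. The two Color-Word measures come from one test, so a correlation of zero between them is unlikely, and the lower part of each range deserves weight.

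**Conclusion.** The point holds in a limited form. Three unranked primary outcomes are each assigned an unadjusted 0.05, and the rule for primary success is left open. Under an any-outcome reading, the stated ANCOVAs carry about 11–14% family-wise error, more than twice the nominal level. The figure of about 19–25% applies only if two contrasts per outcome are tested ungated and both directions are counted. Separately, the three-group test by itself cannot establish that each training beats control.

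The rates rest on assumed outcome correlations of 0 to 0.7, no true effects and T2 as the only primary time point. The T2 assumption fits the two time points in the sample size, and the article lists effects at the 3-month follow-up under the secondary outcome. The power figures rest on f = 0.14.

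**What to change.** In Data analysis and Behavioral data, state: for each of the three primary outcomes at T2, the three-arm ANCOVA F test is done at 0.05/3; only if it is significant are A–C, B–C and A–B tested, at the same 0.05/3. Keep that level for every outcome, and do not raise it by Holm for the pairwise tests. Label all other tests, including those at T3, as secondary without confirmatory claims.

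Alternatively, state that primary success requires all three outcomes. That needs no alpha adjustment across outcomes, but the text should still say whether both trainings must succeed or each is judged on its own.

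The change is to analysis wording and needs no new data. Under the first option the detectable pairwise difference rises by about 15%. If f = 0.14 is what was meant, the plan's calculation needs 18 and 28 per group against 25 planned, so working-memory power falls from about 86% to about 74% before dropout. The Cancer survivors section should give the effect size as a number and restate power at the level actually used; under the all-outcomes option, it should give the power to succeed on all three.

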## Methods

### Design

The study is designed as a randomized stratified controlled trial including three experimental groups (computerized working memory training, exergaming, waiting control group) consisting of pediatric cancer survivors and a healthy control group without intervention (matched for age, gender and socioeconomic status). For cross-sectional evaluation of cognitive performance, cancer survivors and healthy participants will be compared in a baseline assessment. For longitudinal evaluation, only cancer survivors will be randomly assigned to either intervention group A (computerized working memory training), intervention group B (exergaming) or the waiting control group C (see Fig. 1). Cognitive and physical assessment will be carried out before the interventions and the waiting period (baseline assessment; T1) and will be re-performed with all participants after 8-weeks at immediate follow-up (T2) and at a 3-month follow-up (T3). Structural and functional imaging will be performed at each time-point (T1-T3).

